**Trial registration number:**

NCT05587270.

STRENGTHS AND LIMITATIONS OF THIS STUDYLongitudinal assessment of disturbed eating, mental health status, overuse injuries, bone health and symptoms indicative of relative energy deficiency in advanced rock-rock climbers and normal controls.The use of valid and reliable instruments and measurement methods and the large number of potential confounders will improve the internal validity of the estimated associations.The use of dual-energy X-ray absorptiometry complements the participant’s self-report data with objective measurements on bone health.Multivariate statistical analysis will be executed to answer the research questions.One limitation is the use of self-report questionnaires only rather than the combination of self-report and structured interviews.

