Compulsive exercise (CE) consists of maladaptive compensatory behaviours and serves as a strategy for emotion regulation—often closely linked to eating disturbances.^16^ Weight-affecting behaviours in non-clinical groups have demonstrated addictive qualities that aid the understanding of why these behaviours are difficult to change.^16^ Weight-affecting behaviours such as CE have a marked negative effect on psychological and physiological health,^17^ and emotion dysregulation has been suggested to trigger these behaviours.^18^ A previous study of university students indicated a negative association between symptoms of depression and CE for weight control, and a positive association for body dissatisfaction and depression.^19^ These results are in line with studies suggesting excessive exercise to be associated with different psychological traits where poor emotion regulation and compulsivity are two of them.^20^ This may suggest that CE serves as a negatively reinforced behaviour, serving as short-term alleviation of discomfort. Furthermore, exercising for regulation of negative emotion has been consistently identified as a contributory factor to the development and maintenance of EDs.^21^ This contribution does not lie specifically in the presence of negative emotion, but rather in the CE habits that develop as an outlet for these emotions, which in turn is a risk factor for developing disturbed eating. CE is characterised by an inability or unwillingness to cut down or stop the behaviour despite adverse health consequences.

Body dissatisfaction is associated with a drive for thinness,^22 23^ dieting^24^ and DE patterns.^24 25^ The exposure to physical ideals has been seen to have a stronger immediate impact on girls than boys,^26^ and preoccupation with weight, maladaptive methods for weight control and body dissatisfaction are known precursors of more serious clinical EDs, both among athletes and in the general population.^11 12 27^ However, athletes from leanness-focused sports report higher rates of eating disturbances compared with athletes from non-weight sensitive sports.^9^

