Our main hypothesis is that elite and advanced rock climbers will present more DE symptoms compared with controls, with elite rock climbers showing more symptoms than advanced rock climbers. A secondary hypothesis is that rock climbers who report more eating disturbances will present with higher levels of health problems including decreased bone density, CE, depression, body dissatisfaction, menstrual disturbances and more overuse injuries as compared with rock climbers with less symptoms of eating disturbances, as these secondary variables are correlates of EDs.^32^ We expect these patterns to be stable over time. The authors will also examine the gender differences in these categories and expect, for example, to find higher percentages of DE among women than men, following the pattern of the presented literature. At the time of writing, there exists sparse research on the connection between rock climbing, DE and energy deficiency. The presented hypotheses are therefore largely grounded on findings in other sports with similar bodily and/or weight requirements, such as ballet, figure skating and gymnastics. Due to the rapidly increasing popularity of recreational and competitive climbing, longitudinal cohort studies are, therefore, urgently needed to understand the aetiology of health problems related to EDs in rock climbers in particular. Studies that identify risk and prognostic factors are required to develop health promotion and disease prevention strategies, which ultimately can reduce the burden of disease in rock climbers worldwide.

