### Instruments

The first portion of the questionnaire aims to confirm that participants are eligible for inclusion, with a climbing level of advanced or above as classified by IRCRA. Demographic data will be gathered and reported including factors such as age, time practising the sport, amount of weekly training hours, climbing level and gender. Symptoms related to eating disturbances, RED-S, body image, compulsive training, perfectionism, mental health problems, sleep quality, overuse injuries and menstrual dysfunction will thereafter be measured (see table 1).

**Table 1 T1:** Measurements in the CLIMB-study.

Variable	Instrument	Baseline	Follow-up (6 months, 1, 2, 3 and 5 years postbaseline)
Eating disorder symptoms	The Eating Disorders Questionnaire (Fairburn and Beglin, 1994)^33^	X	X
Overuse injuries	The Oslo Sports Trauma Research Centre Overuse Injury Questionnaire (Clarsen *et al*, 2013)^35^	X	X
Perfectionism	The Frost Multidimensional Perfectionism Scale (Frost *et al)*^36^	X	X
Compulsive training	The Compulsive Exercise Test (Taranis *et al*)^39^	X	X
Body dissatisfaction	Body Shape Questionnaire, brief version (Welch *et al*)^41^	X	X
Mental health	Depression Anxiety Stress Scale-21 (Lovibond and Lovibond)^44^	X	X
Sleep quality	The Pittsburg Sleep Quality Index (Carpenter and Andrykowski)^46^	X	X
Symptoms of relative energy deficiency	Relative Energy Deficiency in Sports: RED-S (Edlund Health Q, Edlund, 2020)^50^	X	X
Physical activity and sedentary behaviour	Indicator Questions from the Swedish National Board of Health and Welfare	X*	
Bone density	DEXA	X†	

*Physical activity and sedentary behaviour will only be performed on the control group.

†DEXA will only be performed on a proportion of rock climbers.

DEXA, dual-energy X-ray absorptiometry.

In addition to the web-based questionnaire, bone health using dual-energy X-ray absorptiometry (DEXA) will be measured for climbing participants at baseline.

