### Main exposure variables

DE behaviour, body image, overuse injuries/injuries, indicators of LEA, mental health problems, compulsive training, perfectionism, sleep quality, sedentary behaviour and bone density.

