### Data analysis plan

Multinominal logistic regression analyses will be used to determine the associations between each of the exposures and trajectories of outcomes. The associations as ORs and 95% CIs will be reported. Bivariate models to measure the crude associations between the exposures and trajectories will be built.

The differences between the rock climbers and controls regarding the above-mentioned outcome measure ED will be analysed using multivariate analysis of variance (MANOVA). Both within-group and between-group analysis will be conducted. Further analyses among rock climbers with high ED versus low ED will be compared in relation to bone density, injuries, mental health and symptoms of RED-S. The MANOVA will be used for that purpose. A one-way repeated measures ANOVA will be used to identify changes over the 2-year span in the two groups of rock climbers with high ED versus low ED. In cases where overall significant changes are detected, post hoc analysis will be applied to specify where the between-group differences exist.

Structural equation modelling will be used at a later stage to investigate if the variables body image, injuries, mental illness, sports environment, bone density (from baseline) and EDs can predict injuries.

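### The variables named for the injury model do not include training volume, which the study collects, so its paths from eating disorder and mental illness to overuse injury are open to confounding

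*Protocol article*

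**What the plan says.** The last paragraph of the Data analysis plan in the protocol article describes a later-stage structural equation model that asks whether "body image, injuries, mental illness, sports environment, bone density (from baseline) and EDs can predict injuries". No listed variable is stated to measure training volume. The sports environment item is not defined anywhere and has no instrument in Table 1.

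The Instruments section says that the demographic data gathered and reported include "age, time practising the sport, amount of weekly training hours, climbing level and gender". Neither weekly hours nor time in the sport appears again in the plan. The Main exposure variables section does not list them. It ends with "mental health problems, compulsive training, perfectionism, sleep quality, sedentary behaviour and bone density", and compulsive training there is the Compulsive Exercise Test, a scale of exercise attitudes and behaviour rather than hours.

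For the multinomial regressions, the only model-building step described is this: "Bivariate models to measure the crude associations between the exposures and trajectories will be built". No adjusted model and no covariate is named for any analysis. The strengths and limitations list nevertheless says that "the large number of potential confounders will improve the internal validity of the estimated associations".

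The Outcome section makes overuse injury, measured with the OSTRC-O questionnaire, one of two primary outcomes. As described, the score runs to 100 and is not scaled for hours trained.

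**The concern.** It is an ordinary premise that overuse injury depends partly on how much a person trains. The documents do not state it, so it is an assumption here. If climbers with more eating disturbance or poorer mental health also train more (or less), a model without training volume assigns part of the training effect to those psychological predictors.

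The model is meant to say what predicts injury in climbers. The Introduction wants such results to feed prevention strategies, and the dissemination plan sends them to climbing communities and stakeholders. An ED-to-injury path that partly reflects training volume could misdirect that advice. The stated strength about confounders does not help unless they enter a model: collecting a variable does not adjust for it.

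**Working it through.** **Inputs from the document.** The model's variables are those in the Data analysis plan. Training hours are collected (Instruments). The planned size is about 55 climbers (Sample size). The document gives no correlation between hours and the ED score, and no effect of hours on injury. There is no stated figure to reproduce for this point.

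**Assumptions.** Let *a* be the correlation between training hours and the ED score, and *b* the standardised effect of hours on injury. Let the true direct effect of ED on injury be zero. Take *a* = *b* = 0.2, 0.3 or 0.4.

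**Step 1: spurious path with hours left out.** For a single standardised predictor, the omitted-variable formula gives spurious coefficient = *a* × *b*:

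- 0.2 × 0.2 = 0.04
- 0.3 × 0.3 = 0.09
- 0.4 × 0.4 = 0.16

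If *a* or *b* is zero, the product is zero. If they have opposite signs, the spurious path is negative.

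**Step 2: false-positive rate, two-sided 5% test.** By Fisher's z, the expected test statistic is z = atanh(*ab*) × √(n − 3), and the rejection rate is 1 − Φ(1.96 − z) + Φ(−1.96 − z). With n = 55, √52 = 7.21:

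| *ab* | z | Rejection rate |
|---|---|---|
| 0.04 | 0.29 | 6.0% |
| 0.09 | 0.65 | 10.0% |
| 0.16 | 1.16 | 21.4% |

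The bias does not shrink with recruitment, so the rate rises with n. At an illustrative 200 climbers (not a figure in the document) the rates are 8.7%, 24.5% and 62.0%.

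**Step 3: allow for the listed injuries predictor.** The list has injuries as both predictor and outcome. The natural reading is that earlier injury predicts later injury, though the timing is not stated. Suppose that ED has correlation *ab* with injury at both times, and that earlier and later injury correlate *r* = 0.5 (assumed). Regressing later injury on ED and earlier injury gives

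spurious coefficient = *ab*(1 − *r*) / (1 − (*ab*)²),

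which is 0.020, 0.045 and 0.082, or about half of Step 1. The matching partial correlation is *ab*(1 − *r*) / √[(1 − (*ab*)²)(1 − *r*²)] = 0.023, 0.052 and 0.094. With one covariate, z = atanh(partial correlation) × √(n − 4). At n = 55 (√51 = 7.14), z = 0.17, 0.37 and 0.67, and the rejection rates are 5.3%, 6.6% and 10.3%.

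These steps treat one predictor at a time. The full model has several correlated predictors, so they show the order of magnitude and do not forecast the result.

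**The case against.** The strongest reply is that the sentence names candidate predictors and not a closed adjustment set. Age, gender and climbing level are also collected and also unnamed, and the path diagram of a later-stage model is something an article may leave to the full plan. Calling the bivariate models crude, and citing many potential confounders as a strength, may imply adjusted counterparts. This stands in part: the text does not prove that training hours will be excluded. But it does go as far as naming the model's variables, and nowhere gives training volume a role, so the point concerns the model as stated.

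A reader might infer more, namely that the paths *are* confounded and that the protocol itself ties training volume to its predictors. The document does not support that. The Introduction's phrase "which in turn is a risk factor for developing disturbed eating" is about compulsive exercise habits as an outlet for negative emotion, and the hypothesis "with elite rock climbers showing more symptoms than advanced rock climbers" is about climbing level. Neither is about hours. Nor can it be said that no listed variable reflects exposure to climbing, since the sports environment item is undefined.

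Two further objections stand. Earlier injury, if it is in the model, absorbs part of a stable training effect (Step 3 of the working). And hours are not a clean confounder: eating disturbance may drive training, and the OSTRC-O questionnaire itself scores reduced training due to problems, so current injury may lower current hours. A reader might therefore want the model to separate a direct ED effect from one through training. With ED and hours both measured at baseline, the data do not secure that split.

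**Conclusion.** The point holds in limited form. As named, the injury model omits training volume, the study collects it, and no other adjusted model in the article uses it. The ED and mental-illness paths to a co-primary outcome are therefore open to confounding by training.

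The size rests wholly on assumed values. With links of 0.2 to 0.4, the spurious path is 0.04 to 0.16 SD, with a false-positive rate of about 6% to 21% at 55 climbers. With earlier injury in the model and an assumed correlation of 0.5, it is about 0.02 to 0.08 SD, with a rate of about 5% to 10%. With either link at zero there is no bias. At the low end the problem is negligible. At the high end it could change what is reported.

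The model is a later-stage analysis and does not bear on the main hypothesis, which compares eating symptoms between climbers and controls. The change is worth making because it is cheap and the data are already collected.

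**What to change.** In the Data analysis plan, add baseline weekly training hours and years of climbing to the structural equation model as covariates for injury measured at follow-up, with baseline injury also in the model. Report the ED and mental-illness paths with and without these covariates.

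The cost is about one sentence of text and a few extra parameters, with no new data collection at baseline. The downside is interpretive: training may partly result from eating disturbance or be reduced by current injury, so adjustment can also remove part of a real effect. The adjusted path should be read as a sensitivity check on confounding, not as a separated direct and mediated effect.

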## Ethics and dissemination

All participants will provide informed consent to participate in CLIMB after they had been informed about the purpose and procedure of the study and that it has been approved by the Swedish Ethical Review Authority (reference number: 2021-05557-01).

The dissemination plan is to present our results to the climbing and sport communities, in peer-reviewed scientific journals, at congresses and to stakeholders with influence in the development of climbing environments.

### Study status

The manuscript reports the protocol (ClinicalTrials.gov NCT05587270) for an ongoing study for which participants are currently ongoing. Data collection has been initiated and baseline analyses are planned to commence during 2023.

## Discussion

Climbing is a weight sensitive sport where athletes generally benefit from a lean body shape and low weight^6^—a risk factor for eating disturbances. There are very few studies regarding eating disturbances among rock climbers. A study by Joubert *et al*, examining DE among international sport lead rock climbers, displayed that 6.3% of male and 16.5% of female climbers had DE.^30^ Similarly, a study examining amenorrhoea among female competitive climbers showed that 15.8% of female climbers had amenorrhoea. The IFSC recently released a statement to counteract this development of the sport. Due to the over-representation of eating disturbances reported in other lean sports and the poor treatment prognosis, early detection and prevention of eating disturbances and energy deficiency is essential, especially considering the growing popularity of the sport.

There are several major strengths of CLIMB. The first is the use of longitudinal data within several domains related to disturbed eating and mental health issues by using validated questionnaires, reducing misclassification of outcomes. The few studies published at this time, on this topic, do not consider multiple mental health parameters that CLIMB intends to address, such as perfectionism, sleep habits, body dissatisfaction and CE. It is the first study on rock climbers which also includes a control group, providing vital context on disease prevalence. CLIMB will be representative of the advanced climbing community at large in Sweden as it includes a wide age span of both genders who climb at advanced and elite levels around Sweden, markedly decreasing the risk of selection bias. Additionally, this large sample of climbers contributes to ensuring external validity. The use of DEXA complements the participant’s self-report data with objective measurements on the effects that relative energy deficiency is associated with, establishing a point of action and initiative to prevent and treat afflicted athletes.

One limitation of our study is that we are using a non-random convenience sample that may not be representative to advanced rock-rock climbers in an international perspective. We have aimed to include the whole advanced level rock-climbing community in Sweden aged 15 years and older, which is the rationale for how the participants were recruited. According to the Swedish Climbing Association, there were 15 409 climbers affiliated to a climbing club in 2022. It is unknown, however, how many climbers are of an advanced or higher level, and thus eligible for participating in the study. Another potential limitation is the use of self-report questionnaires only which yield subjective data. Although the authors will encourage all participants to fill out all surveys using communication strategies at baseline and throughout the follow-up surveys, there is an undeniable risk of increased drop-out rates with each passing survey.

The climbing-concerned scientific community is at the beginning of forming a paradigm around this subject. The many facets of this study make CLIMB invaluable in gaining a holistic view on each participant as well as on group levels, which ultimately contributes to developing and implementing evidence-based interventions around the globe.
